## Screening Assessments

| Table 3. Screening Assessments    |                                                                                                                                                                                                                                                                                                                                                               |
|------------------------------------------|---------------------------------------------------------------------------------------------------------------------------------------------------------------------------------------------------------------------------------------------------------------------------------------------------------------------------------------------------------------|
| Medical History And Physical Examination | Includes body weight, vital signs                                                                                                                                                                                                                                                                                                                             |
| Eye examination                          | Eye examination by an ophthalmologist at screening will be done on indication. Patients with preexisting ophthalmologic disorders (eg, diabetic or hypertensive retinopathy) should receive periodic ophthalmologic exams during Peg-IFN therapy. Peg-IFN treatment should be discontinued in patients who develop new or worsening ophthalmologic disorders. |
| Clinical Chemistry                       | ASAT, ALAT, bilirubin, creatinine, urea, sodium, chloride, potassium, calcium, phosphorus, prothrombin time, alkaline phosphatase, total protein, albumin, BUN, uric acid, cholesterol, triglycerides, glucose                                                                                                                                                |
| Hematology                               | Leukocyte count, differential WBC, red blood count, platelets                                                                                                                                                                                                                                                                                                 |
| Immunology and Special Chemistry         | HBeAg, anti-HBe, HBsAg, anti-HBs
anti-HIV, anti-HCV, anti-HDV, Alfa-fetoprotein, ceruloplasmin, alfa1-antitrypsin, ferritin
Only for patients at risk without previous data being available: AMA, ANA, ASMA, thyroid peroxidase antibodies.                                                                                                             |
| Virology                                 | Quantitative HBV-DNA measurement                                                                                                                                                                                                                                                                                                                              |
| Thyroid Function Tests                   | TSH, free T 4                                                                                                                                                                                                                                                                                                                                      |
| Urinalysis                               | Dipstick with subsequent microscopic evaluation if positive for hemoglobin                                                                                                                                                                                                                                                                                    |
| Chest X-Ray                              | Will be done during screening (Not necessary if (1) a chest X-ray available to the investigator has been obtained within the past 12 months and (2) the patient's pulmonary disease has remained clinically stable.)                                                                                                                                   |
| Electrocardiogram                        | Only for anyone with a history of pre-existing cardiac disease.                                                                                                                                                                                                                                                                                               |
| Liver Biopsy (a)              | Performed at start of the study and repeated after 48 weeks.                                                                                                                                                                                                                                                                                                  |
| Fibroscan (b)                 | Performed at start of the study and repeated after 48 weeks.                                                                                                                                                                                                                                                                                                  |
| Liver Imaging (ultrasound)               | Performed at screening or start of the study, repeated after 48 weeks and on indication.                                                                                                                                                                                                                                                                      |
| Liver Imaging (CT or MRI)                | Only for patients suspected to have hepatic neoplasia.                                                                                                                                                                                                                                                                                                        |
| HCG Pregnancy Test                       | For women of childbearing potential a negative urine (or serum) HCG test needs to be documented within 24 hours prior to the first dose.                                                                                                                                                                                                                      |

(a) When a participant has objections against a second liver biopsy at week 48 ,he or she can refuse it. The participant will than not be excluded from the study.

(b) A fibroscan measures the liver stiffness, expressed in kilopascals (kPA)

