### Study design:

This is a three arm open-label prospective randomized controlled trial. 150 patients will be enrolled into the study after assessment of eligibility. All patients must have documented HBsAg positivity for longer than 6 months, HBeAg negativity, anti-HBe positivity, HBV DNA < 20,000 IU/mL and ALT < 5 \* upper limit of normal. Patients with a Child Pugh class B or C will be excluded. Group 1 will consist of patients treated with Peg-IFN and adefovir, group 2 will consist of patients treated with Peg-IFN and tenofovir and group 3 will consist of untreated controls. Patients in group 1 and 2 will receive medication for the period of one year. For enrolment into the study a liverbiopsy at time of enrolment is compulsory and is advisable at end of treatment (week 48).

**Study population:** The study population will consist of 150 patients chronically infected with hepatitis B virus with low viral load and HBeAg negativity.

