### 3. STUDY DESIGN

This is a three arm open-label prospective randomized controlled trial. (n=150) The trial is designed to compare the efficacy of treatment with Peg-IFN and ADF or Peg-IFN and TDF versus no treatment for clearance of the HBsAg in chronic hepatitis B patients with low viral load.

Patients will be enrolled into the study after assessment of eligibility. Group 1 will consist of patients treated with Peg-IFN 180µg once weekly and ADF 10mg once daily (standard doses), group 2 will consist of patients treated with Peg-IFN 180µg once weekly and TDF 300mg (equivalent to 245 mg tenofovir disoproxil) once daily (standard doses) and group 3 will consist of untreated patients as negative controls.

The trial consists of a screening period of approximately 4 weeks, a 48 week treatment period, a 24 week follow-up period and a long term follow up period of 5 year. A schematic overview of the study design is presented in table 1 and 2 (see appendix).

150 patients will be randomized in a 50:50:50 ratio to one of the treatment groups.

Randomization will be stratified to genotype A to optimize balance between treatment groups. All patients will receive medication for the period of 48 weeks. For enrolment into the study a liver biopsy at time of enrolment is compulsory for patients selected in the treatment groups. For enrolment of patients that are selected in the non-treatment group a liverbiopsy is optional but not compulsory for participation. In patients selected in the treatment group a second liver biopsy at week 48 is recommended for evaluation of therapeutic responses and to guide any further possible therapy. Due to the burden of undergoing a liver biopsy, the second liver biopsy is not compulsory to take part into the study. Patients that are selected in the non treatment group will not undergo a biopsy at week 48. Patients will be clinically monitored intensively according to the assessment schedule (table 1). In the long term follow up period patients will be clinically monitored each year.

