#### **7.1.3. Other study parameters**

Baseline characteristics will be documented of all patients. Age, weight, sex, medical history, cause of infection, interferon naïve, previous treatment, histology activity index, ISHAK fibrosis score, prescence of cirrhosis, ethnicity will be documented.

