## Schedule of Assessments

Table 1. Schedule of Assesments

| Assessment/ Procedure                                   | Screening
(weeks) | Study treatment Period Peg-INF and ADF, Peg-IFN and tenofovir or no treatment
(weeks) |       |   |   |   |   |   |    |    |    |    |    |    |    | Follow-up
(weeks) |   |   |    |    |    |    |
|---------------------------------------------------------|----------------------|------------------------------------------------------------------------------------------|-------|---|---|---|---|---|----|----|----|----|----|----|----|----------------------|---|---|----|----|----|----|
|                                                         |                      | B                                                                                        | Day 3 | 1 | 2 | 4 | 6 | 8 | 12 | 18 | 24 | 30 | 36 | 42 | 48 | 2                    | 4 | 8 | 12 | 16 | 20 | 24 |
| Study weeks                                             | -4 to 0              |                                                                                          |       |   |   |   |   |   |    |    |    |    |    |    |    |                      |   |   |    |    |    |    |
| Informed consent, medical history                       | X                    |                                                                                          |       |   |   |   |   |   |    |    |    |    |    |    |    |                      |   |   |    |    |    |    |
| Physical examination                                    | X                    | X                                                                                        |       | X | X | X |   | X | X  |    | X  |    | X  |    | X  |                      | X |   | X  |    |    | X  |
| Liver biopsy (preceding 12 months)                      | X                    |                                                                                          |       |   |   |   |   |   |    |    |    |    |    |    | X  |                      |   |   |    |    |    |    |
| Urine or serum pregnancy test a              |                      | X                                                                                        |       |   |   | X |   | X | X  | X  | X  | X  | X  | X  | X  |                      | X | X | X  | X  | X  | X  |

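### Section 3, the Summary and the biopsy rows of Tables 1 and 3 state different liver-biopsy rules for the untreated control arm

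*Protocol*

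**What the plan says.** Section 3 (Study Design) treats the arms separately:

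- Enrolment, treated arms: "a liver biopsy at time of enrolment is compulsory for patients selected in the treatment groups".
- Enrolment, controls: "For enrolment of patients that are selected in the non-treatment group a liverbiopsy is optional but not compulsory for participation".
- Week 48, treated arms: a second biopsy is recommended but not compulsory.
- Week 48, controls: "Patients that are selected in the non treatment group will not undergo a biopsy at week 48".

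Three other places do not separate the arms:

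- **Table 1 (Schedule of Assessments)** marks the liver biopsy at screening and at week 48, under the column heading "Study treatment Period Peg-INF and ADF, Peg-IFN and tenofovir or no treatment". The row carries no arm footnote.
- **Table 3 (Screening Assessments)** says of the liver biopsy: "Performed at start of the study and repeated after 48 weeks". Its note (a) lets a participant decline the second biopsy and stay in the study. It does not mention controls.
- **Summary, Study design**, straight after the three groups and the one-year treatment period are described: "For enrolment into the study a liverbiopsy at time of enrolment is compulsory and is advisable at end of treatment (week 48".

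**The concern.** A control patient's biopsy schedule depends on which page is read. Someone working from the biopsy rows of Tables 1 and 3 would ask an untreated patient for a week-48 biopsy that Section 3 says will not take place. Someone working from the Summary would treat the enrolment biopsy as a condition of entry for a patient for whom Section 3 makes it optional.

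The protocol itself counts liver biopsy among the burdens of taking part, and Section 3 gives that burden as the reason for not making the second biopsy compulsory. At stake are the burden on controls, uniform conduct across sites, and which arms will have histology data.

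**Working it through.** **Step 1: size of the control arm.** Section 3 states "150 patients will be randomized in a 50:50:50 ratio to one of the treatment groups", so 150 / 3 = 50 controls. Section 4.4 can be reproduced as a check on that figure:

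- Inputs: 44 per group, proportions 0.20 and 0.01, two-sided Fisher's exact test, significance level 0.05, 10% dropout.
- Exact enumeration gives power of 80.6%, against 81% stated.
- Dropout allowance: 44 / (1 − 0.10) = 48.9, that is 49, against 50 stated.

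Both agree closely with the plan, so 50 is the right denominator.

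**Step 2: the passages side by side, for controls only.**

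| Source | Enrolment biopsy | Week-48 biopsy |
|---|---|---|
| Section 3 | Optional | Not done |
| Summary | Compulsory, no arm limit | Advisable at the end of treatment; unclear for untreated patients |
| Table 1 | Marked, no arm limit | Marked, no arm limit |
| Table 3 | Done at start, no arm limit | Repeated, no arm limit; may be refused |

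The firm conflict at week 48 is Section 3 against Tables 1 and 3. The firm conflict at enrolment is Section 3 (optional) against the Summary (compulsory). Note (a) does not resolve the first: a right to refuse presupposes that the procedure is offered.

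The tables do carry limits on other rows. Chest X-ray, CT/MRI and ECG are confined to selected patients, and the pregnancy test to women of childbearing potential. None of those limits is by arm, so they show that a limit could have been written, not that its absence here was intended.

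**Step 3: number of control biopsies at week 48.**

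- Section 3: 0.
- Tables 1 and 3 read literally: at most 50.
- With the planned 10% dropout applied to controls: 50 × 0.9 = 45. This is an assumption, because Section 4.4 attributes the dropout partly to Peg-IFN side effects, which controls do not have.
- With a refusal proportion r, which the protocol does not give: 45 × (1 − r). That is 45 at r = 0, 22.5 at r = 0.5 and 0 at r = 1.

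**Step 4: enrolment.** The number of controls for whom a biopsy is required is 0 of 50 under Section 3 and 50 of 50 under the Summary. The Table 1 row label refers to the preceding 12 months, which suggests that a recent biopsy may count. Fifty required need not mean 50 new procedures.

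**Step 5: statistical consequences.** The primary endpoint is HBsAg below 0.05 IU/mL, a blood measurement. Nothing in the Section 4.4 calculation uses histology. The predictor analysis in Section 9.1 concerns response to the two combination regimens. None of these changes with the biopsy rule for controls.

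**The case against.** The best reply is that the protocol does give a complete rule. Section 3 covers all four combinations of arm and time point, and the same paragraph then sends the reader to Table 1, so anyone arriving from there has just read the exception for controls. Table 1 is one grid shared by three arms, and a missing footnote is a drafting gap. No passage gives the tables precedence over Section 3.

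Much of this stands, and it limits the point to a wording conflict. It does not remove it: no passage gives Section 3 precedence either, Table 3 has a biopsy note that leaves controls out, and the Summary's enrolment sentence contradicts Section 3 on its face.

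A reader might infer more, but the documents do not support it:

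- **That any baseline biopsy in a control breaches Section 3.** It does not, because that biopsy is optional there. Only requiring it conflicts.
- **That the Summary also contradicts Section 3 at week 48.** It says only that the biopsy is advisable at the end of treatment, which can be read as meaning treated patients.
- **That Section 7.1.3 obliges controls to be biopsied**, because it says "Baseline characteristics will be documented of all patients" and lists histology scores. Documenting characteristics can mean recording what is available, and the sentence concerns baseline only.
- **That a biopsy request would cost control retention.** Nothing in the protocol links the two, and the second biopsy can be refused without leaving the study.

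**Conclusion.** The inconsistency is real and lies in current text. For controls, Section 3 conflicts with Tables 1 and 3 at week 48 and with the Summary at enrolment. Its size is 0 against a theoretical ceiling of 50 week-48 biopsies. The ceiling assumes that the table rows are applied literally to every randomised control, with no dropout and no refusal, so it is not an expected count. A reader might take it to mean that 50 controls will be biopsied; the protocol gives no basis for that.

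The sample size, the power and the HBsAg endpoint are untouched. The matter is one of participant burden and uniform conduct. It is worth correcting because the procedure is invasive and the correction is cheap. The conflict also does not show that Section 3 holds the right rule and the tables the wrong one; that is a clinical decision and is not judged here. The consent pages are not available, so what controls are told about biopsy cannot be assessed.

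**What to change.** Reconcile Section 3, the Summary and the biopsy rows of Tables 1 and 3, so that each states the same rule, by arm, for the enrolment biopsy and for the week-48 biopsy: required, offered or not done. An arm-specific footnote on the two table rows and a matching clause in the Summary would do this. The sponsor decides which rule applies. Notify sites of the clarified wording, preferably before any control reaches week 48.

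The cost is a few lines of text and a site notice. No analysis or sample-size change follows.
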